#### Phase 2: A theory-based IPC intervention development

This component aims to identify behavioral change components necessary for developing a behavioral change intervention by pooling the findings obtained in Phase 1 and a systematic review of IPC implementation interventions in LMICs. The intervention development process will consist of the following four components:

##### Identifying behavioral change components

All behavioral change components under the “Theoretical Domains Framework (TDF)” (36) will be listed and components that need improvement will be identified. The TDF domains identified in Phase 1 will be prioritized.

##### Systematic literature review

A systematic literature review will be conducted, providing the necessary resources to develop the intervention for this study. The review aims to identify intervention models used to promote IPC practices among healthcare workers in LMICs. The review protocol will be registered in PROSPERO, an international database of prospectively registered systematic reviews (37). Peer-reviewed studies and grey literature, reporting IPC interventions among healthcare workers and patients in LMICs, published in English will be included. The extracted data will be analyzed and identified common themes or patterns related to intervention models targeting behavioral change in IPC practices among healthcare workers. The detail of the review protocol and findings will be reported elsewhere.

##### Develop intervention components

The behavioral change components identified in Phase 1 will be matched with the intervention components identified in the systematic review. As a guide to design this IPC intervention, the Behavior Change Wheel (BCW) model will be used, which follows eight steps, including defining the problem in behavioral terms, selecting the target behaviors, specifying the target behaviors, identifying what needs to change and intervention functions, policy categories, behavior change techniques, and the mode of delivery (38).

##### Validate the behavior change intervention

Once the intervention is developed, a national consultative workshop in collaboration with the MoH in Cambodia and Lao People’s Democratic Republic will be conducted to validate the intervention. This workshop aims to summarize the findings from gap analysis, relevant interventions from the systematic review, and the developed interventions. Non-governmaental organizations (NGOs) and key stakeholders working on IPC in each country, representative from district, provincial, and national hospitals will be involved to obtain their feedback on the development of the intervention.

#### Phase 3: Pilot intervention

Once the validation is done, the developed intervention will be piloted at the same three hospitals selected in Phase 1 in each country. The representative from each hospital will be approached to inform them the contents of the pilot intervention. Following that, 15 healthcare workers from each of the three selected wards at the national hospitals, 10 from each of the three selected wards at the provincial hospitals, and seven from each of the three selected wards at the district hospitals will be recruited to participate in the pilot intervention (Table 2).

**Table 2 tab2:** Sample of participants participate in the pilot intervention in each country (Cambodia and Lao People’s Democratic Republic).

Health system level	Number of hospitals^a^	Number of healthcare workers per ward	Number of wards	Total sample
National	1	15	3	45
Provincial	1	10	3	30
District	1	7	3	21
Total	3	32	9	96

a For the national and provincial hospitals, we will select intensive care units, surgery units, and medical wards. We will select surgery units, maternal and child health wards, and medical wards for district hospitals.

#### Phase 4: Intervention’s feasibility and acceptability assessment

Subsequently, a post-pilot evaluation will be conducted to assess the feasibility and acceptability and identify barriers and challenges in implementing the developed IPC intervention (32, 35). Additionally, post-pilot direct observation of hand hygiene and low-level disinfection of equipment practices among healthcare workers at the same selected wards in Phase 1 of the selected national, provincial, and district hospitals will also be performed. The assessment will comprise IDIs with healthcare workers and KIIs with representative from each hospital in Cambodia and Lao People’s Democratic Republic. For IDIs, 36 healthcare workers in each country (15 from the national hospitals, 12 from the provincial hospitals, and nine from the district hospitals) will be randomly selected from the pool of 96 healthcare workers participating in the pilot intervention (Phase 3; Table 3).

**Table 3 tab3:** Sample of participants for the feasibility and acceptability assessment in each country (Cambodia and Lao People’s Democratic Republic).

Health system level	Number of health facilities^a^	Number of healthcare workers	Number of key informants	Total sample
National	1	15	1	16
Provincial	1	12	1	13
District	1	9	1	10
Total	3	36	3	39

IDI, in-depth interview; KII, key-informant interview.

a For the national and provincial hospitals, we will select intensive care units, surgery units, and medical wards. We will select surgery units, maternal and child health wards, and medical wards for district hospitals.

After documenting the results of the feasibility and acceptability assessment of the pilot intervention, a national dissemination workshop will be conducted in each country. The results of the pilot intervention and the findings from the feasibility and acceptability study will be shared during the workshop. This workshop will be used as a platform to discuss this intervention’s potential strengths and limitations. This can be used for planning future scaling-up purposes. Attendees will include those involved with IPC-related policy including MoH, representative from the provincial health department, and operational district office, NGOs working on IPC, and representative from the district, provincial, and national hospitals in each country.

### Tool development

#### For gap analyses

A standardized WHO’s hand-hygiene observation tool for direct observation (Supplementary material 1) will be adapted for this study (39). The observation form contains two main elements: a header and an observation grid. The header will enable the observers to record the time, date, and location of the selected wards. The observation grid allows observers to record the data to compute the hand hygiene compliance of the healthcare workers.

An observation form will be adapted from an existing study (Supplementary material 2) (40) to observe the low-level disinfection of equipment compliance among healthcare workers. Low-level disinfectants are used to disinfect noncritical items that come into contact with skin. According to the national guidelines on IPC for healthcare facilities, the equipment includes bedpans, toilets, urinals, blood pressure cuffs, electrocardiogram leads, thermometers, stethoscopes, beds, and bedside tables (22, 23).

In Phase 1, IDIs using an interview guide (Supplementary material 3) with healthcare workers will be conducted to understand the factors influencing their hand-hygiene practices. A topic guide from an existing study (41) will be adapted, containing questions derived from 14 theoretical domains to capture multiple-level determinants of health-related behavioral change. Furthermore, healthcare workers will be asked how the COVID-19 pandemic has impacted their hand-hygiene practices.

Additionally, A KII topic guide (Supplementary material 4) will be developed to understand the perspective of key stakeholders about the gap in IPC implementation and practices among healthcare workers in both countries, adapting questions from an existing study (42). Questions on the impact of the COVID-19 pandemic on HAI prevention and control in each country will also be included in the interview guide.

#### For assessing the intervention’s feasibility and acceptability

In Phase 4, hand hygiene and low-level disinfection of equipment observations will be conducted using the same forms developed in Phase 1. Additionally, the topic guide questions (Supplementary material 5) will be adapted from a relevant study (43) to explore the feasibility of the developed intervention and if there are any issues with the intervention and its implementation process. Healthcare workers’ experiences with the developed intervention during the pilot Phase will also be explored to assess the feasibility and acceptability of the developed IPC intervention. Post-pilot KIIs among representative from each hospital who will participate in the pilot phase will be conducted. The interviews aim to explore their perspective on the intervention piloted in Phase 3. The questions (Supplementary material 6) will be adapted from the literature (44).

### Training and data collection procedures

Before the data collection in Phases 1 and 4, the study coordinators will train data collectors in a two-day workshop, followed by another day for study tool pretesting. Data collectors will include staff and graduate students from the University of Health Sciences (UHS) in Cambodia and the Lao Tropical and Public Health Institute (Lao-TPHI) in Lao People’s Democratic Republic. The training will cover direct observations and interview techniques, including confidentiality, privacy, and data quality control.

For hand-hygiene observation, training materials will be adapted from WHO’s training tools (45). The adapted training materials will include PowerPoint presentations and an educational video of healthcare workers performing care in hospital settings. The training will include observation of healthcare workers’ hand-hygiene practices at the selected hospitals. Each observation session will last approximately 20 min (+10 min buffer time, depending on the observed activity) (26). The WHO’s five moments of hand hygiene will be applied: (1) before touching patients or patient surroundings, (2) before a clean/aseptic procedure, (3) after body fluid exposure risk, (4) after touching a patient, and (5) after touching the patient’s surroundings (26). The hand-hygiene actions will be recorded when either handwashing with soap and water or alcohol hand rubbing is observed according to the five moments indicated above. To obtain reliable estimates of the compliance rate, WHO recommends at least 200 opportunities for each ward per observation period (26). The observations will be conducted during the regular working hours of 8: 00 AM–12: 00 PM and 1: 00 PM–5:00 PM.

Similarly, observers will be trained to observe practices among healthcare providers. Healthcare providers will be considered practicing low-level disinfection of equipment if they disinfect non-critical medical equipment (i.e., bedpans, electrocardiogram leads, stethoscopes, blood pressure apparatus, thermometers, pulse oximeters, glucometers, beds, and bedside tables) with approved disinfectants before and after the equipment comes to contact with patients.

Study coordinators will also train data collectors on qualitative data collection techniques using interview guides for IDIs and KIIs. In Phase 1, the IDIs questions will be guided by the TDF (46) to assess factors influencing healthcare workers’ hand-hygiene practices. However, rigidly applying the TDF may result in specific determinants or gaps being overlooked. Therefore, the interviewers will be instructed to be open to any responses from the participants so that the responses will be distinct from the pre-determined TDF domains. Moreover, the interviewers will be trained to use simple languages so that the participants can comprehend the questions correctly.

The hand hygiene and low-level disinfection of equipment observation training in Phase 4 will include the same contents as in Phase 1. Additionally, the study coordinators will train interviewers on conducting IDIs and KIIs, including using neutral wording and probing questions.

Following the training in Phases 1 and 4, the interviewers and observers will spend one morning pretesting the topic guides for IDIs and KIIs and the observation form on hand hygiene and low-level disinfection of equipment in one hospital in the capital city of each country. In the afternoon, all the interviewers and observers will reflect on their experience with the study tools and provide feedback.

Potential participants from each selected hospital will be invited through the heads of the selected hospitals and wards and asked them for signed informed consent. Each interview will take approximately 45–60 min to complete. The interviews will be audiotaped, and notes will be taken during the interviews with the participants’ permission. The samples and sampling procedures will be similar in Cambodia and Lao People’s Democratic Republic.

### Data management

Data on hand hygiene and low-level disinfection of equipment observations on paper forms and subsequently enter them into Microsoft Excel 2016 (Microsoft Corporation, Redmond, WA, United States). The study coordinators will upload the audio-recorded IDI and KII data files into a computer folder. The research team will transcribe the audio files in the respective country’s national language (e.g., Khmer and Lao) and store them in another folder. The team will then translate the transcripts into English and keep them in a separate folder. All documents will be password-protected by the study coordinators. The translated transcripts will be anonymized, and unique identification numbers will be assigned instead of personal identifiers to protect the participant’s privacy and confidentiality.

### Data analyses

#### Qualitative data analyses

The study team will transcribe audio recordings from IDIs and KIIs in Phases 1 and 4 verbatim. The transcriptions will then be translated into English. All qualitative data analyses will be performed using NVivo 12 software. For the IDIs in Phase 1, the analyses will follow three steps – coding, generating specific beliefs/themes, and identifying the relevant domains (47).

##### Coding interview transcripts

Two study team members will independently code the transcripts into the 14 domains of TDF using thematic analyses. They will meet and review their coding and definitions of the codes, accompanied by quotes under each code. If there is a disagreement with the coding, the two coders will discuss it and reach a consensus.

##### Generating specific beliefs/themes

One team member will generate specific beliefs/themes for the coded interview quotes in all TDF domains. The second team member will double-check the accuracy of the specific beliefs/themes generated by the first team member. A specific belief/theme is defined as the participant’s responses underlying a similar theme that suggests a barrier or enabler of hand hygiene compliance (41).

##### Identifying relevant theoretical domains

TDF domains through consensus between the two analysts will be identified, judging them based on three factors (47–49). Firstly, the TDF domains relevant to healthcare workers’ hand hygiene compliance if belief/theme statements appear with high frequencies across the interviews will be considered. Secondly, the TDF domain relevant if conflicting beliefs/themes exist will also be considered. Thirdly, the domains will be consided relevant if there is evidence of strong beliefs/themes that may impact hand hygiene practices among healthcare workers. These three factors will be simultaneously considered during the analyses to determine the theoretical domains.

Similarly, the recorded KIIs in Phase 1 and IDIs and KIIs in Phase 4 will be analyzed following the coding manual for qualitative researchers developed by Johnny Saldaña (50) and thematic analyses introduced by Braun and Clarke (51). The framework approach involves familiarizing with the transcription data, generating initial codes, searching for themes, reviewing themes, defining and naming themes, and producing the report (51).

#### Quantitative data analyses

In Phases 1 and 4, hand hygiene and low-level disinfection of equipment compliance rates will be calculated using the number of times healthcare workers followed the appropriate behaviors divided by the total number of observed opportunities and multiplied by 100. A simple tabulations using Stata 17 (Stata Corporation, Texas, United States) will be conducted to summarize the compliance rate by healthcare worker type (doctors, nurses, or midwives). Student’s *t*-tests of the mean difference in hand hygiene and low-level disinfection of equipment compliance rate in Phase 1 (before the intervention) and Phase 4 (after the intervention) will be performed.

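### The before-after comparison tests an unadjusted compliance rate, so a shift between phases in the mix of professions, hand-hygiene moments or equipment items could pass for a change in behaviour

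*Protocol article*

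**What the plan says.** Under Quantitative data analyses, compliance in Phases 1 and 4 is "the number of times healthcare workers followed the appropriate behaviors divided by the total number of observed opportunities", expressed as a percentage. A tabulation will "summarize the compliance rate by healthcare worker type (doctors, nurses, or midwives". The phases are then compared by Student's t "tests of the mean difference in hand hygiene and low-level disinfection of equipment compliance rate in Phase 1 (before the intervention) and Phase 4". The article names no covariates, strata, weights or unit of analysis for that test.

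On the data available:

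- **Ward.** The tool section says of the hand-hygiene form: "The header will enable the observers to record the time, date, and location of the selected wards".
- **Moment.** Under Training and data collection procedures the "five moments of hand hygiene will be applied", and a hand-hygiene action is recorded when handwashing or "alcohol hand rubbing is observed according to the five moments indicated above". This implies that the moment is captured, though the form itself is in a supplement.
- **Profession.** It must be captured for the planned tabulation.
- **Number of opportunities.** The article cites a WHO recommendation of at least 200 per ward and observation period. This is a floor. No quota by profession or moment is described.
- **Setting.** Phase 4 observes the same wards as Phase 1, with the same forms (Phase 4; tool section).

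**The concern.** A crude rate is an average of stratum rates weighted by however many opportunities each stratum supplied in that phase. Sessions last about 20 minutes, with up to 10 more depending on the activity seen, and the observed workers are not said to be the same in both phases. The weights can therefore differ between phases. If compliance also differs by profession, moment or item, the crude rate moves with no change in behaviour, in either direction.

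In a controlled study, a mix shift common to both arms would largely cancel. Here the same three hospitals per country are observed before and after with no comparator, so the reading of the difference depends on the two samples being comparable. The limitations paragraph in the Discussion covers the Hawthorne effect, working hours and generalisability, but not a change in mix.

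**Working it through.** The article states no effect size, power or expected rate for this comparison, so there is no figure to reproduce. The check asks how large the artefact could be.

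**Inputs from the article.** Nine wards per country (Table 2); a floor of 200 opportunities per ward, giving 9 × 200 = 1,800 per country and phase; 62.4% compliance in a previous study cited in the Discussion, used here only as a baseline.

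**Assumptions.** Stratum gaps of 10 to 30 points; 5 to 20% of opportunities moving between strata; a two-sided 5% test on individual, independent opportunities. The article gives none of these.

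**Formula.** Crude rate = Σ(share × stratum rate). If stratum rates are unchanged and a share s moves between two strata whose rates differ by g, the spurious change is g × s.

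**One case in full.** With g = 0.30 and s = 0.10 the change is 0.03. At 1,800 per phase, SE = √[(0.624 × 0.376 + 0.654 × 0.346)/1,800] = 0.0160, so the ratio is about 1.87. The chance of rejecting is Φ(1.87 − 1.96) + Φ(−1.87 − 1.96) ≈ 47%.

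**Range** (probability of a significant result with no behaviour change; nominal 5%):

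| Gap (points) | Share moved | Spurious change (points) | 200 per phase | 600 per phase | 1,800 per phase |
|---|---|---|---|---|---|
| 10 | 5% | 0.5 | 5.1% | 5.4% | 6.1% |
| 20 | 10% | 2.0 | 7.0% | 11.1% | 23.8% |
| 30 | 10% | 3.0 | 9.6% | 19.1% | 46.6% |
| 20 | 20% | 4.0 | 13.3% | 30.5% | 70.8% |
| 30 | 20% | 6.0 | 24.4% | 59.1% | 96.6% |

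The three sample sizes are one ward, one hospital (3 × 200) and one country at the floor.

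**Profession examples.** With doctors at 40% and nurses and midwives at 70%, a fall in the doctors' share from 30% to 20% moves the crude rate from 0.3 × 40 + 0.7 × 70 = 61% to 0.2 × 40 + 0.8 × 70 = 64%. With three professions at 50/65/70%, a mix going from 20/60/20 to 30/50/20 moves it from 63.0% to 61.5%.

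**Moment example.** With rates of 30/50/80/70/40% over the five moments, a mix going from 30/10/10/30/20 to 20/10/15/35/20 moves the crude rate from 51.0% to 55.5%. At 1,800 per phase, SE = √(2 × 0.249/1,800) = 0.0166 and t ≈ 0.045/0.0166 = 2.7.

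**Ward.** Simulating nine wards with rates from 45 to 80% and 200 to 400 opportunities each, drawn at random in each phase, the spurious change has an SD of 1.0 point, with 95% within about 2.0 points. With equal ward counts, or equal weight per ward, this part is zero.

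**After adjustment.** Holding the mix fixed makes the artefact zero when stratum rates are unchanged.

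**The case against.** The strongest reply is that this is a condensed article and an unseen analysis plan may adjust. That stands in part: silence about further analyses is no fault. But the article does more than stay silent. It fixes a crude estimator and a test that takes no covariates.

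Four stronger readings are tempting, and the article does not support them.

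- **That the test pools all wards.** The rate formula suggests this, but the unit of the t-test is not given. If ward rates were compared, ward mix would cancel. The mix of professions and moments within wards would not.
- **That the two phases are haphazard samples.** The article does not describe them so. Each ward is observed for 14 days (Discussion), in the same wards, with the same forms and training content, in regular working hours. These features make large shifts less likely, without fixing the mix.
- **That profession is ignored.** The table by profession would show unchanged rates in the 61% to 64% example, so an attentive reader could spot the artefact. The tested difference would still contain it.
- **That a false positive is to be expected.** The t of 2.7 rests on invented rates, a shift out of the lowest-compliance moment into the two highest, and 1,800 opportunities treated as independent. It shows what is possible, not what will happen.

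Two further limits stand. The five moments concern hand hygiene only. For disinfection the parallel variable is equipment item, and the article does not show that the form records it. Also, the objectives are gap analysis, intervention development, and feasibility and acceptability, so this test is not named as primary.

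**Conclusion.** The point holds in limited form. The stated comparison is an unadjusted t-test on a crude rate in an uncontrolled before-after design, and nothing described keeps the mix of professions, moments or items the same. The artefact ranges from 0.5 points (negligible) to 6 points under the assumed gaps and shifts. The rejection rates also assume independent opportunities and the 62.4% baseline. Moment is the strongest part, because no analysis by moment is stated. Profession is partly covered by the table. Ward is the weakest, because the same wards are revisited and ward mix may cancel, depending on the unit of analysis. The change is worth making because this is the only quantitative before-after comparison the article states, but the feasibility and acceptability objectives do not depend on it.

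**What to change.** State the unit of analysis. Keep the crude rate and the table by profession. Add, for hand hygiene, a phase effect from a regression (for example logistic) with main-effect terms for ward, profession and moment. For equipment disinfection, replace moment with item type if the form records it, and confirm this before Phase 4. Use standard errors that allow for clustering; with nine wards per country the clusters are few, so a small-sample correction is advisable. Base the before-after interpretation on the adjusted effect.

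Do not standardise directly over the full cross-classification. Ward by profession by moment gives 9 × 3 × 5 = 135 cells, about 13 opportunities each at 1,800 per phase (1,800/135 = 13.3) if spread evenly, and some cells would probably be empty. Main-effect terms avoid this.

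The cost is slightly more analysis and a result less simple to explain than the crude rate. No new sites or participants are needed and, for hand hygiene, no new data if the form records the moment as the text implies.
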